### Sample size {19}

Objective 1: Assuming that the mean and variance of the area of lesions (as determined by the SkinScan3D method) are the same for two clinicians, then the expected width of a 95% confidence interval (CI) for the concordance correlation coefficient for a given number of lesions examined is shown in Table 1. Therefore, with at least 50 participants with 3 lesions each (150 lesions), we will get a precise estimate of the CCC. To address overinterpretation of the concordance, we will complement the R-squared with additional metrics that capture accuracy more directly, including Bland-Altman plots to assess agreement and systematic bias, mean absolute error, and root mean square error. These measures will allow us to evaluate both correlation and the magnitude and direction of differences between methods.

Objective 2: We will roll out the refined SS3D intervention to 100 participants (50 patients at UCI; 25 at JOOTRH; 25 at Homa Bay). All providers will complete quantitative surveys. We anticipate recruiting providers (up to n=10), clinic administrators and key decision makers (up to n=5) who will participate in semi-structured interviews at each clinic. The final sample of semi-structured interviews will be determined by the point at which thematic saturation is achieved.

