### Who will be included in each analysis {27b}

All enrolled patients with complete paired measurements will be included. Analysis for Objective 1 will be at the lesion level (up to 150 lesions from 50 participants). For Objective 2, the usability and implementation outcome analyses will include all providers who completed the relevant questionnaires. The cost analysis will include all patients enrolled during the study period.

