## Figures and Tables

**Figure 1 F1:**
[figure not shown]
Manual bidimensional measurement for Kaposi sarcoma skin lesions using the AIDS Clinical Trial Group (ACTG) method (not drawn to scale). Three representative morphologies are shown: (A) oval, (B) round, and (C) irregular. Lesion area is calculated as the product of thelongest diameter (d_1_) and the longest perpendicular diameter (d_2_), both measured in millimeters using a ruler. This method does not capture lesion height, volume, or color.

**Table 1. T2:** Expected width of 95% confidence intervals (precision)

Number of lesions	CCC = 0.8	CCC = 0.9
50	0.67 to 0.88	0.83 to 0.94
100	0.72 to 0.86	0.85 to 0.93
150	0.73 to 0.85	0.86 to 0.93

**Table 2. T3:** Summary of cost measures and associated data sources

Cost type	Elements	Data sources
**Start-up**	Training materials; training expenses (trainer fees, staff time spent in training)	Project expense reports; staff/civil service salaries
**Implementation**	Training expenses; technical assistance; fidelity monitoring; community outreach	Project expense reports
**Personnel**	Time/salaries of healthcare personnel, supervisors, and administrative staff	Direct observations; salaries; interviews
**Patient**	Transportation; other out-of-pocket expenses including childcare; time losses	Patient surveys; local average wages
**Supplies**	Consumables utilized or dispensed on a per-patient basis, particularly front-end adaptors	Clinic and project expense reports
**Capital**	SkinScan3D equipment utilized in clinics	Manufacturing and shipping costs
**Utilities**	Space/storage, internet, electricity, other overhead costs associated with SS3D	Clinic and project expense reports

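### The 150-lesion precision in Table 1 is for independent lesions, but Objective 1 has three lesions in each of 50 participants and nothing allows for the clustering

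*Protocol article*

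**What the plan says.** Under Sample size {19}, the protocol article states one assumption for Objective 1: "Assuming that the mean and variance of the area of lesions (as determined by the SkinScan3D method) are the same for two clinicians". It points to Table 1 for the resulting precision ("the expected width of a 95% confidence interval (CI) for the concordance correlation coefficient for a given number of lesions examined is shown in Table"), and concludes that "with at least 50 participants with 3 lesions each (150 lesions), we will get a precise estimate of the CCC".

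Table 1 is indexed by number of lesions (50, 100, 150). Its last row gives 0.73 to 0.85 at CCC 0.8 and 0.86 to 0.93 at CCC 0.9. Its first row gives 0.67 to 0.88 and 0.83 to 0.94.

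Section {27a} computes one CCC and one R-squared per method from a pooled plot of clinician 1 against clinician 2. Section {27b} sets the unit of analysis: "Analysis for Objective 1 will be at the lesion level (up to 150 lesions from 50 participants". Section {5} says that the analysis plan is contained in {27a} to {27d}. None of those sections mentions correlation between lesions of the same participant or names a method for the confidence interval of the CCC.

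**The concern.** Three lesions on one person are unlikely to carry as much information as three lesions on three people. They share disease stage, treatment, skin tone, the visit and the two clinicians (Participant timeline {18}; {25a}). Background {9a} itself says that reading lesion borders by color contrast is harder in skin of color, which would be a participant-level source of measurement error.

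If sizes or errors are positively correlated within a person, 150 clustered lesions estimate the CCC less precisely than 150 independent ones. The CCC is a primary outcome, and Table 1 is the only quantitative support for the size of Objective 1. What is at stake is the stated precision, and the honesty of any interval later computed as if lesions were independent.

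**Working it through.** **Inputs.** From the protocol: 95% confidence; CCC 0.8 and 0.9; 50, 100 and 150 lesions; 50 participants with 3 lesions each; equal means and variances for the two clinicians, so that the CCC equals the Pearson correlation. Not in the protocol, so assumed: the within-participant correlations of lesion size and of measurement error.

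**Step 1: reproduce Table 1.** The Fisher z interval is tanh(atanh(CCC) ± 1.96/√(n−3)), with n the number of lesions. For n = 150 and CCC 0.8: atanh(0.8) = 1.0986; 1.96/√147 = 0.1617; tanh(0.9370) = 0.734 and tanh(1.2603) = 0.851.

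| n | CCC 0.8 computed | Table 1 | CCC 0.9 computed | Table 1 |
|---|---|---|---|---|
| 50 | 0.671-0.882 | 0.67-0.88 | 0.829-0.942 | 0.83-0.94 |
| 100 | 0.716-0.861 | 0.72-0.86 | 0.855-0.932 | 0.85-0.93 |
| 150 | 0.734-0.851 | 0.73-0.85 | 0.864-0.927 | 0.86-0.93 |

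All 12 limits match (the lower limit at n = 100, CCC 0.9 is 0.8547 before rounding). Using √(n−2) also matches all 12, so the exact formula is not identified, but both versions treat every lesion as an independent unit.

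**Step 2: the limit of the loss.** If lesions within a person were perfectly correlated in size and error, 150 lesions would carry the information of 50. That is Table 1's 50-lesion row: 0.67-0.88 and 0.83-0.94.

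**Step 3: intermediate cases by simulation.** 50 participants with 3 lesions each, 20,000 runs per scenario, normal data. True size has a share *a* of its variance common to the participant. Each clinician's error has a share *b* common to that participant. Error is scaled by √((1−CCC)/CCC) to give the target CCC. Effective n = 1/SD(z)² + 3, where z = atanh(estimated CCC). Coverage is that of the interval from Step 1 with n = 150. Results at CCC 0.8:

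| Size/error correlation | Effective n | Coverage | 95% interval at effective n |
|---|---|---|---|
| 0/0 | 151 | 95.0% | 0.734-0.851 |
| 0.3/0 | 141 | 94.3% | 0.731-0.853 |
| 0.3/0.3 | 129 | 93.1% | 0.728-0.855 |
| 0.5/0 | 125 | 92.5% | 0.727-0.855 |
| 0.7/0 | 110 | 90.3% | 0.721-0.859 |
| 0.5/0.5 | 104 | 89.2% | 0.718-0.860 |
| 0.7/0.7 | 78 | 83.5% | 0.702-0.868 |

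Check on one row: at 0.7/0.7, SD(z) = 0.1157, so 1/0.1157² + 3 ≈ 78.

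CCC 0.9 behaves almost the same: 0.863-0.927 at 0.3/0, 0.855-0.931 at 0.5/0.5 (coverage 89.4%) and 0.847-0.935 at 0.7/0.7 (coverage 83.8%).

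**Step 4: a caution on the shortcut.** The usual design effect 1 + (3−1) × ICC, with the ICC of lesion area put in, overstates the loss. At an area correlation of 0.3 it gives 1.6, whereas the simulated variance inflation is 1.07 with independent errors and 1.17 with errors also correlated at 0.3. The ICC that belongs in that formula is that of each lesion's contribution to the CCC estimate, not of lesion area.

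**The case against.** **The loss may be small.** This stands in part. With correlations of 0.3 or below, coverage stays at 93% or better and the interval hardly changes. The loss becomes material from about 0.5 upward. The protocol gives no value, so neither end of the range can be ruled out.

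**The arithmetic is right and the table is labelled by lesions.** This stands. A reader might infer that Table 1 is miscalculated; it is not. The fault is the sentence that reads its 150-lesion row as the precision of 50 participants with three lesions each.

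**No interval method is named, so a clustered interval is not excluded.** This stands as far as it goes: a lesion-level unit of analysis does not fix the variance estimator. Under-coverage in the final analysis is therefore implied, not written. It cannot be left to a separate plan, because section {5} places the whole analysis plan in {27a} to {27d}.

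**The decision rule uses point estimates.** Sections {16} and {27a} call the method with the higher CCC the more reproducible, and clustering hardly shifts either estimate.

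**Stronger readings.** A reader might infer that every comparison of the two methods will be over-confident. The protocol does not support that. It plans no interval-based comparison, and both methods measure the same lesions. If the two CCC estimates are positively correlated, ignoring that pairing is conservative for their difference and works against the effect of clustering. The net direction has not been computed. Nor has under-coverage been shown for the subgroups in {27d}: one person's lesions may fall in different morphology or size strata, which would reduce clustering within a stratum.

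**Conclusion.** The point holds, and should be fixed. The precision stated for 50 participants with three lesions each is that of 150 independent lesions, and the design delivers less under any positive within-participant correlation that affects the CCC estimate.

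The mechanism is certain, because Table 1 reproduces in full. The size is an assumption. Over size/error correlations from 0.3/0 to 0.7/0.7, the width of the CCC 0.8 interval goes from 0.117 as planned to between 0.122 (0.853 − 0.731) and 0.166 (0.868 − 0.702). These figures rest on normal data with errors independent between clinicians; skewed lesion areas were not examined.

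A reader might also infer that Objective 1 is too small. The protocol sets no width or power target that the wider intervals would miss, so that does not follow.

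**What to change.** 1. Restate Table 1 for 50 participants with three lesions each over a stated range of within-participant correlation, with the independence case as one end and the present 50-lesion row as the other. Amend the sentence in Sample size {19} to match.
2. In {27a}, prespecify the 95% confidence interval for each CCC, and for the paired difference in CCC between SS3D and the ruler, either by a bootstrap that resamples participants (keeping all their lesions, both clinicians and both methods together) or by a variance-components CCC with participant and lesion effects. Keep the lesion as the unit of measurement in {27b}, and add that the participant is the cluster.

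The cost is a slightly less favourable stated precision and a little more analysis. No extra patients and no change to data collection are needed, so the change can be made while recruitment continues, before any analysis.

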**Methods::**

PRIME-KS is a multicountry prospective mixed-methods study with two clinical objectives. Objective 1 is a cross-sectional diagnostic accuracy study comparing SS3D with ruler-based measurement in 50 adults with KS (150 lesions) across sites in Kenya and Uganda. Two clinicians independently measure three lesions per participant using both methods. The primary outcomes are concordance correlation coefficient (CCC) for inter-rater reproducibility, and co-efficient of determination for accuracy. Objective 2 is a non-randomized before-and-after pilot study in 100 patients at three sites, evaluating device usability, acceptability, appropriateness, and feasibility using validated instruments, along with time-and-motion studies and activity-based micro-costing. Prior to these clinical objectives, a formative study used focus group discussions, discrete choice experiments, and human-centered design workshops to refine the SS3D device and protocols with end-user input.

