### Explanation for the choice of comparator {9b}

The comparator is the current standard of care for KS lesion measurement: manual ruler-based assessment using ACTG criteria, which calculates lesion area as the product of the longest perpendicular diameters (Figure 1).^1, 2^ This method was selected because it is the globally recognized standard for KS treatment response assessment used in clinical trials. Comparing SS3D against this established method will determine whether SS3D offers superior reproducibility and accuracy for clinical decision-making.

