### Outcomes {16}

#### Objective 1 (Reproducibility and Accuracy)

##### Primary outcomes:

(1) Concordance correlation coefficient (CCC) for inter-rater reproducibility of KS lesion area measurement. The CCC will be calculated separately for SS3D and for the ruler-based method, based on measurements by two independent clinicians of the same three lesions per participant. The measurement variable is projected lesion area (mm^2^). The method with the higher CCC will be considered the more reproducible. (2) Coefficient of determination (R-squared) for each measurement method, assessing the proportion of variation attributable to true lesion size versus random measurement error.

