### Statistical methods

Statistical methods for primary and secondary outcomes {27a}

#### Objective 1

We will plot a graph for each measurement method. Each graph’s x-axis will represent measurements from clinician 1 and y-axis will represent measurements from clinician 2. For each graph, we will calculate the concordance correlation coefficient (CCC) and coefficient of determination (R-squared). The CCC measures reproducibility (agreement) between clinicians for each method. The method with the higher CCC will be considered the more reproducible, and the method with R-squared closer to 1 will be considered the more accurate. We will also visualize agreement between methods graphically using Bland-Altman plots, and report the mean difference and 95% limits of agreement. To provide a more robust assessment, we will also report mean absolute error and root mean square error to capture the magnitude of differences between methods.

#### Objective 2

System Usability Scale (SUS) scores will be computed following standard scoring procedures (score contributions from items summed and multiplied by 2.5, yielding a score range of 0 to 100). Device usability will further be normalized to generate percentile ranks and graded as either acceptable (score above 68), marginal, or not acceptable. AIM, IAM, and FIM scores will be presented as means, standard deviations, and ranges. Qualitative data collected from semi-structured interviews will be transcribed, coded, and thematically analyzed to identify sub-themes and themes related to SkinScan3D implementation in routine clinical settings. Data triangulation will be applied to cross-validate findings from interviews and direct observation to ensure rigor and validity of the qualitative analysis.

For the cost analysis, we will summarize data to estimate the total program cost of SS3D per patient and per visit, excluding research costs. Costs will be broken down by the categories in Table 2 to identify key cost drivers.

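### The "precise estimate" of the CCC in {19} allows for sampling of lesions only and sets systematic clinician differences to zero, so it does not extend to reproducibility of the method among clinicians in general

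*Protocol article*

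**What the plan says.** Section {19} of the protocol article derives "the expected width of a 95% confidence interval (CI) for the concordance correlation coefficient for a given number of lesions examined". The condition is "Assuming that the mean and variance of the area of lesions (as determined by the SkinScan3D method) are the same for two clinicians". Table 1 then gives, for 150 lesions, 0.73 to 0.85 at a CCC of 0.8 and 0.86 to 0.93 at a CCC of 0.9. From this {19} concludes that "with at least 50 participants with 3 lesions each (150 lesions), we will get a precise estimate of the CCC".

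Under Outcomes {16} the CCC is the inter-rater measure, computed for each method "based on measurements by two independent clinicians of the same three lesions per participant". Section {27a} plots one clinician against the other and applies the rule "The method with the higher CCC will be considered the more reproducible". Section {27b} sets the unit of analysis at the lesion. Section {5} says that the statistical analysis plan is contained in {27a} to {27d}; those sections have no clinician component. The abstract describes the study as carried out "in 50 adults with KS (150 lesions) across sites in Kenya and Uganda". How many clinicians will take readings over the whole study is not stated.

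**The concern.** A CCC between raters falls short of 1 for two reasons: random reading error and systematic differences between raters. More lesions reduce the uncertainty about the first. They do not reduce the uncertainty about the second, which depends on how many clinicians are observed. Table 1 removes the second source by assumption and then describes the result as precise without qualification.

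For the particular clinicians who take part, and provided they do not differ systematically, this is defensible. But {16} and {27a} use the CCC to call a method more reproducible, and that is a statement about clinicians who will use it later. If few clinicians take part, an interval built on lesion count can be too narrow for that purpose, and nothing in the reported figure would show it. This is a separate matter from the correlation of three lesions within one patient, which Table 1 also leaves out.

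**Working it through.** **1. Reproducing Table 1.** With equal means and variances, the Fisher-transformed interval is tanh(atanh(CCC) ± 1.96/√(n − 2)), where n is the number of lesions, treated as independent.

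| n | CCC 0.8 | CCC 0.9 |
|---|---|---|
| 50 | 0.673 to 0.881 | 0.830 to 0.942 |
| 100 | 0.717 to 0.861 | 0.855 to 0.932 |
| 150 | 0.734 to 0.851 | 0.865 to 0.927 |

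All 12 limits agree with Table 1 to two decimals. (Using n − 3 also reproduces the table.) Lesion count is therefore the only source of uncertainty in it.

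**2. Adding a clinician component.** Let lesion variance be L, clinician bias variance B and reading-error variance E. The population CCC is L/(L + B + E). The documents give none of these, so the following values are assumptions: log area, lesion SD 0.7 (L = 0.49), reading noise 15% (E = 0.0225), three sites with one clinician pair each, 150 lesions in all.

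| Assumed bias SD | B | Population CCC | B/(B + E) | Coverage of a Table 1-type interval |
|---|---|---|---|---|
| 5% | 0.0025 | 0.49/0.515 = 0.951 | 10% | about 91% |
| 10% | 0.01 | 0.49/0.5225 = 0.938 | 31% | about 74% |
| 20% | 0.04 | 0.49/0.5525 = 0.887 | 64% | about 42% |

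Coverage is by simulation; repeat runs differed by about two percentage points. With no bias, coverage is 95%. At 20% bias the estimated CCC ranges over roughly 0.74 to 0.96, against a Table 1-type interval of 0.85 to 0.92. At 10% the range is 0.89 to 0.96, against 0.915 to 0.955. In the same scenarios, an interval that includes a clinician variance component had coverage of about 93% to 95%.

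**3. A second set of assumptions, on Table 1's own scale.** Population CCC 0.8, 150 lesions, 4,000 runs, with clinician bias making up a given share of the non-lesion variance. Entries are the central 95% range of the estimate, with the coverage of the usual CCC interval in brackets.

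| Bias share | 1 pair | 4 pairs |
|---|---|---|
| 0% | 0.73 to 0.85 (95%) | 0.73 to 0.85 (95%) |
| 10% | 0.71 to 0.85 (90%) | 0.73 to 0.85 (93%) |
| 25% | 0.65 to 0.87 (72%) | 0.70 to 0.86 (83%) |
| 50% | 0.57 to 0.91 (34%) | 0.64 to 0.90 (61%) |

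**4. More lesions do not cure it.** Take one pair, CCC 0.8 and a 25% share: L = 0.8, B = 0.05, E = 0.15. With unlimited lesions the CCC is 2(0.8)/(2 × 0.95 + d²) = 1.6/(1.9 + d²), where d is the pair's bias difference, with variance 2B = 0.10. The 97.5% point of d² is 0.10 × 5.02 = 0.50, giving 1.6/2.40 = 0.67. At d near 0 it is 1.6/1.9 = 0.84. The range stays at 0.67 to 0.84.

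**The case against.** The arithmetic of Table 1 is right, its assumption is stated openly, and it is stated for SS3D only. SS3D computes area automatically ({25a}), through an adaptor that fixes angle and distance ({15a}), so its rater effect may well be small. At a 5% bias SD the loss of coverage is minor. This stands, and it limits the size of the point for SS3D. It does not help the ruler, for which a CCC is also to be reported.

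One pair per site is a reading, not a statement in the protocol. Two clinicians per participant is stated; the same two throughout a site is not, and nothing excludes rotation. This also stands, and it is why the figures above are conditional.

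A reader might infer that the plan promises a precise comparison of the two methods and fails to deliver it. The documents do not support that. Section {19} claims precision for one CCC. The sentence in {9b} that the comparison "will determine whether SS3D offers superior reproducibility and accuracy" is rationale, not a precision statement. The same clinicians use both methods, so part of any clinician effect may cancel.

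Nor is it shown that the choice of clinicians would decide the ranking. Under assumed values (three sites, one pair each, equal noise), a ruler bias of 20% against 5% for SS3D puts the ruler first in about 5% of runs. With 10% against 5% it is about 21%, but there the true CCCs nearly tie (0.94 and 0.95), and four rotated clinicians per site still give 13%.

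Finally, the protocol does not call clinician bias the ruler's chief weakness. It lists inter-observer variability among several, and does not say whether that variability is systematic.

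**Conclusion.** The point holds in a limited form. The unqualified claim of precision in {19} is valid only for the participating clinicians, and only if they do not differ systematically. The CCC is used for a wider conclusion about the method. How far the interval is too narrow cannot be settled from the protocol, because the number of clinicians and the bias variance are not given. It ranges from negligible (bias SD 5%, coverage about 91%) to serious (20%, about 42%) for one pair at each of three sites, and shrinks with more pairs. The study is labelled exploratory, which lowers the stakes but does not make the statement correct. The change is worth making because it is cheap and easier to make early in recruitment.

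**What to change.** - **{19}:** state that Table 1 holds only for the clinicians who take part and only if they do not differ systematically. Give the planned number of clinicians or pairs per site.
- **{25a}:** record a clinician identifier on every reading, for both methods.
- **{27a}:** take the CCC interval for each method from a variance-components model, or from resampling, that includes clinician as well as participant. This also deals with the three lesions per patient.
- **Optional:** where a site already has more than two trained clinicians, rotate the pairs. This adds no readings, but it needs scheduling and may not be possible at small clinics.

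No extra patients or readings are needed. The reported intervals will be wider, and with few clinicians the clinician component will itself be imprecisely estimated, which the report should say. Uganda has been recruiting since 1 April 2026, so identifiers for readings already taken should be recovered now if they were not recorded, and any rotation there would begin mid-study. Kenya has not started. A substantive change goes through the ethics review described in {31}.
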